### Intervention

The RuralKidsGPS model uses the circle of coordination for CYP with medical complexity, which places the CYP and their needs at the centre of the system for integrating care (Figure 2). Families are guided by local PCCs who are responsible for facilitating care integration and establishing the circle of coordination which is formed by leads from the hospital, community, and family.

**Figure 2 F2:**
[figure not shown]
RuralKidsGPS Circle of Coordination (adapted from Cohen, et al. 2011).

The PCCs work with families to:

Understand their personalised needs.Develop and implement an integrated family-centred shared care plan.Build capacity for family self-management and deliver practical holistic support.

The PCCs also work with treating teams to identify opportunities to integrate and share care among central units and local teams, deliver virtually enabled care, streamline appointments, avoid unnecessary hospitalisations, and prevent avoidable ED attendances.

### Impact evaluation

#### Health Service Use

A cohort-level evaluation of health utilisation (primary outcome) will be conducted. A cohort of children receiving the RuralKidsGPS will be recruited from the participating LHDs. Routinely collected administrative health data for these children will be requested and linked by an independent group, the NSW Centre for Health Record Linkage (CHeReL) (Figure 3). Using this deidentified linked data, we will compare the change and trend in health utilisation of children (ED presentations, hospital admissions, and outpatient (OP) appointments) who received RuralKidsGPS, to that of a matched comparison group.

**Figure 3 F3:**
[figure not shown]
Sources of data for linkage.

The comparison group will be identified using the linked administrative health data (ED presentations, hospital admissions, and OP appointments) and frequency matched with 20 children (to each case) by clinical diagnosis, year of birth, sex, local health district who and meet the eligibility criteria for health service use within the past 6 months (outlined in the Study Cohort section above) but who did not access RuralKidsGPS. A population-level evaluation will also be conducted which will include all CYP in the 4 health districts meeting the inclusion criteria.

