### Study cohort

The study population includes CYP with medical complexity aged 0 to 18 years, referred for care coordination, who meet the following criteria:

– A diagnosis expected to last at least 12 months– And if ≥ 6months of age, frequent use of health services within the last six-month period, defined as:Two or more ED presentations, ORHospital admission for seven days or more, ORTwo or more outpatient appointments.

A cohort of CYP meeting these criteria and referred for care coordination, their parents and guardians, and clinical and non-clinical staff involved in the planning and/or delivery of the RuralKidsGPS model of care, will all form a part of the study cohort.

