#### Impact Evaluation Analyses

Based on local data from the participating LHDs, we aim to recruit 400 children across the four LHDs. We will match each case by 20 controls, resulting in a total of 8,000 controls. This will provide 90% power to detect a 20% difference in the number of health service use occasions, including outpatient visits and hospital admissions between intervention and comparison groups. Having 400 cases will also provide the power of 90% to detect a within-group 20% decrease in the number of health service use occasions. This sample size will also allow us to detect a clinically important difference (4.36 points) for child health related quality of life in children post- vs pre-intervention change in the PedsQL4.0 Total Scale Score [9].

We will calculate rate of health service use (e.g. ED, hospital admissions and OP visits) in person-years for the intervention and comparison groups during the baseline (3 years prior to enrolment) and the intervention period (12 months after enrolment), respectively. To assess the effectiveness of this intervention, we will conduct multivariable Poisson (negative binomial if over-dispersion is present) regression analysis with intervention status (intervention versus comparison) as the main independent variable and the rate of health service use (ED, hospital admissions and OP visits, separately and combined) during the intervention period as the outcome variable.

To examine how health service use changes over time between intervention and comparison groups, we will analyse rates of health service use during baseline and intervention periods using mixed effect Poisson regression models, including the interaction term between intervention status and time (after RuralKidsGPS implementation versus before RuralKidsGPS). In all regression analyses, we will control for participant socio-demographics (e.g., age at enrolment, sex, Aboriginal and Torres Strait Islander status, socio-economic status) and clinical factors (e.g., type and severity of health conditions), and baseline rate of health service use. Considering potential clustering effect by site, we will use the generalised estimating equations (GEE) approach in the regression analysis.

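### Time since diagnosis is neither matched nor a named covariate, and a 3-year average baseline cannot remove a difference in illness stage between cases and comparators

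*Protocol article*

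**What the plan says.** Under Study cohort, cases are children "referred for care coordination, who meet the following criteria". The diagnosis criterion looks forward only: "A diagnosis expected to last at least 12 months". No minimum or maximum time since diagnosis is set. Children aged 6 months or more must also show "frequent use of health services within the last six-month period".

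Under Health Service Use, comparators are taken from the linked administrative records, "frequency matched with 20 children (to each case) by clinical diagnosis, year of birth, sex, local health district". They must also "meet the eligibility criteria for health service use within the past 6 months" and not have used the service.

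Under Impact Evaluation Analyses, rates are computed for the "baseline (3 years prior to enrolment) and the intervention period (12 months after enrolment"). The primary model regresses the 12-month rate on intervention status. A second model tests the interaction of intervention status with time. All models adjust for demographics and for "clinical factors (e.g., type and severity of health conditions), and baseline rate of health service use". The article aims for 400 cases and 8,000 comparators, with 90% power for a 20% difference.

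**The concern.** The two groups enter by different routes. A case enters when someone refers the child; a comparator enters because the records fit. Nothing in the matching or in the named covariates aligns them on how far into the illness they are.

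The planned safeguard is the baseline rate, but it is a 3-year average. A child diagnosed 3 months before enrolment has a low average, nearly all of it from before the illness, followed by a year of heavy use. A long-standing patient with the same average stays roughly level. Conditioning on the average, or dividing by it, treats these children as alike.

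If the groups differ in the share of newly diagnosed children, the error falls on both between-group estimates that serve the primary aim. With newer cases, a working service looks weaker than it is. With newer comparators, a service with no effect looks beneficial. A larger sample does not reduce either error.

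**Working it through.** **The plan's own figure.** The 90% power can be neither confirmed nor refuted, because alpha, mean rate and dispersion are not stated. At two-sided 0.05 it is attainable, for example with a mean of 2 events per year and dispersion 1.19. It is not in dispute here. It sets the yardstick: hiding a true rate ratio of 0.80 completely needs a bias factor of 1/0.80 = 1.25.

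**Assumptions (none is in the article).** Established patients use 6 services per year throughout. Newly diagnosed children are 0-6 months past diagnosis (mean 0.25 year). They use *g* per year before onset, 12 per year for 6 months after it, then 6. The service has no effect.

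**Expected rates for a newly diagnosed child.**
- 3-year baseline: (2.75*g* + 0.25 × 12)/3. With *g* = 1 this is 5.75/3 = 1.92; with *g* = 3 it is 11.25/3 = 3.75.
- Following year: 0.25 × 12 + 0.75 × 6 = 7.5.

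**Before/after ratio of ratios.** With newly diagnosed shares *p* (cases) and *q* (comparators):

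[7.5*p* + 6(1−*p*)]/[7.5*q* + 6(1−*q*)] ÷ [*b p* + 6(1−*p*)]/[*b q* + 6(1−*q*)], where *b* is the baseline rate above.

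For 30% v 15% and *g* = 1: the post ratio is 6.45/6.225 = 1.036, the baseline ratio is 4.775/5.3875 = 0.886, and the result is 1.17.

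| *p* v *q* | Post ratio alone | Before/after, *g* = 1 | Before/after, *g* = 3 |
|---|---|---|---|
| 15% v 15% | 1.00 | 1.00 | 1.00 |
| 20% v 15% | 1.01 | 1.05 | 1.03 |
| 30% v 15% | 1.04 | 1.17 | 1.10 |
| 40% v 15% | 1.06 | 1.31 | 1.18 |
| 15% v 30% | 0.97 | 0.86 | 0.91 |

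Most of the distortion therefore comes from the baseline, not from the follow-up year.

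**Simulation (400 cases, 8,000 comparators).** This adds between-child variation and the requirement of at least 2 events in the last 6 months in both groups. It fits a negative binomial model adjusted for the 3-year rate. With *g* = 1 and no effect, the adjusted ratio was 1.04-1.05 at 20% v 15%, 1.14-1.17 at 30% v 15%, 1.23-1.28 at 40% v 15%, and 0.87-0.90 at 15% v 30%. With *g* = 3 it was about 1.03-1.04, 1.11 and 1.18 for the first three.

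**Effect on a true 0.80.** At 40% v 15% with *g* = 1: 0.80 × 1.28 = 1.02. With *g* = 3: 0.80 × 1.18 = 0.94. At 20% v 15%: 0.80 × 1.05 = 0.84.

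**A second set of assumptions.** Here diagnosis falls 6 months before enrolment, use before diagnosis is 25% of the established rate, and use afterwards equals the established rate. The baseline-adjusted estimate of a true 0.80 was 0.93 at 30% v 10% and 1.08 at 50% v 10%.

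**After the fix.** A stage covariate measured without error returned 0.99-1.01 with no effect and 0.80 with a true 0.80. In the second set it returned 0.79-0.81. With 10% misclassification of stage, about 40-60% of the bias remained: a factor of 1.16 becomes 1 + 0.4 × 0.16 = 1.06 to 1 + 0.6 × 0.16 = 1.10.

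**The case against.** A reader might infer that newly diagnosed referrals are in fact set against long-standing patients, and that illness stage will by itself cancel a true 20% benefit. The article supports neither. It describes cases only as referred, frequent users with a lasting diagnosis, and its account of the service points towards established complex illness. It gives no distribution of time since diagnosis in either group. With equal shares the bias is zero. Full cancellation needs roughly 40% v 15% newly diagnosed and very low use before onset. All of this stands.

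There are partial safeguards. Matching on diagnosis and birth year together largely fixes duration for conditions present from birth. Comparators meet the same 6-month use criterion, but new and long-standing patients can both satisfy it. Severity adjustment might absorb some of the difference, though severity is not stage. The monthly plots and the interrupted time series could show a steeper rise before enrolment in one group, but they would not correct the primary rate ratio.

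The covariate list is given as examples, so an analysis plan could add time since diagnosis, and its absence from a condensed article is not an omission in itself. What remains is the design as fixed: a matching set stated without such a qualifier, and a 3-year average baseline that cannot do this job.

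A fifth matching factor would strain 20:1 matching in rural districts, and look-back beyond 3 years is not described. Both objections are accepted in the fix.

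**Conclusion.** The point holds as a conditional risk of bias. Time since diagnosis is uncontrolled, and the 3-year baseline adjustment cannot remove a between-group difference in illness stage. The resulting bias in the primary rate ratio and the group-by-time ratio is about 4-5% at 20% v 15% newly diagnosed, about 10-16% at 30% v 15%, and about 17-28% at 40% v 15%. The lower end of the two larger ranges applies when use before onset is 3 per year and the upper end when it is 1 per year. The direction depends on which group is newer and is unknown. These sizes rest on assumed rates and shares; the article gives neither. A modest imbalance dilutes or exaggerates the effect slightly. Only a large one reaches the 20% difference that the study is meant to detect.

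**What to change.** Within the 3-year linked baseline window, derive for both groups the time from the first record of the matching diagnosis to the index date. Code it as under 6 months, 6-12 months, 1-3 years, or already present at the start of the window. Then:

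- report its distribution by group;
- add it as a covariate to the post-period model;
- add it, with its interaction with time, to the before/after model.

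Matching on it is optional, where cells allow.

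The cost is one derived variable and a few lines in the analysis plan. It needs an index date for comparators, which the before/after comparison requires in any case, and a rule for which diagnosis starts the clock in a child with several. The limit is accuracy: a first record is not a date of diagnosis, and with 10% misclassification about 40-60% of the bias may remain. The balance table should therefore be read alongside the adjusted estimate.

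### Cases under 6 months need no prior use, but year-of-birth matching lets comparators selected for frequent use into their comparison group, so the infant part of the primary comparison is not like with like

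*Protocol article*

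**What the plan says.** **Cases.** The Study cohort section asks every child for "A diagnosis expected to last at least 12 months". The second criterion is conditional on age: "if ≥ 6months of age, frequent use of health services within the last six-month period". Frequent use means two or more ED presentations, an admission of seven days or more, or two or more outpatient appointments. A child under 6 months therefore qualifies on referral and diagnosis, with no use requirement.

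**Comparators.** The Health Service Use section (paragraph after Figure 3) takes comparators from linked administrative data and frequency matches 20 to each case on diagnosis, "year of birth, sex, local health district who and meet the eligibility criteria for health service use within the past 6 months", with a pointer to the criteria "outlined in the Study Cohort section above) but who did not access RuralKidsGPS". The age condition is not repeated.

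**Analysis.** Impact Evaluation Analyses plans 400 cases: "We will match each case by 20 controls, resulting in a total of 8,000 controls". The effectiveness model regresses the 12-month rate after enrolment on intervention status. A second model uses the interaction of group and period, with a baseline of 3 years before enrolment. All regressions adjust for socio-demographics (age at enrolment is an example), type and severity of condition, and baseline rate of use.

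**The concern.** From 6 months of age both groups pass the same use filter. Below 6 months cases do not pass it, and some or all of their comparators do.

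The pointer to the Study cohort section leaves two readings: comparators under 6 months are exempt as cases are, or every comparator must show the use. The coarse age match causes trouble on both. A birth year spans 12 months, so a comparator can be almost a year older than the case. For example, a case born in December and enrolled the following March is 3 months old, while a child born in January of the same birth year is then 14 months old. That child enters the pool only by frequent use.

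Prior use predicts later use, and later use is the primary outcome. In this stratum comparators are partly selected on a predictor of the outcome and cases are not. Part of the rate ratio then reflects the entry rule and not the service.

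**Working it through.** **Stated figures.** 400 × 20 = 8,000 agrees with the plan. The 90% power for a 20% difference cannot be reproduced, because event rate, dispersion and alpha are not given. At two-sided 0.05 it is reached with dispersion of about 0.57, 1.19, 1.50 and 1.65 at 1, 2, 4 and 8 contacts a year, so it is attainable. This point does not depend on it.

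**Assumed inputs (none is in the document).** Contacts follow a gamma-Poisson model with mean m per 6 months and shape k. The use criterion is simplified to N ≥ 2 contacts in 6 months. There is no treatment effect, and infant cases have the same underlying rate as the unselected pool.

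**1. No comparator exempt.** The expected rate given n contacts is (n + k)/(k/m + 1). With m = 2 and k = 1, N is geometric, so E[N | N ≥ 2] = 2 + 2 = 4. The comparators' mean rate is (4 + 1)/(0.5 + 1) = 3.33, and the infant rate ratio is 2/3.33 = 0.60.

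| m | k | Infant rate ratio |
|---|---|---|
| 1 | 0.5 | 0.37 |
| 2 | 1 | 0.60 |
| 4 | 1 | 0.71 |
| 4 | 2 | 0.83 |
| 6 | 2 | 0.89 |

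Simulations at 4 contacts a year and shape 1 gave 0.52-0.57.

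**2. Exemption carried over.** Assume uniform births, case age uniform over 0-6 months, and comparators drawn on the case's enrolment date. Then 25% of infant cases have no same-birth-year child aged 6 months or over. On average 32% of those already born are that old. With m = 2 and k = 1, P(N ≥ 2) = (2/3)² = 0.444, so the older children who enter weigh 0.32 × 0.444 = 0.142 against 0.68 for exempt infants. They form 0.142/0.822 = 17% of the pool.

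The pool's mean rate is (0.68 × 2 + 0.142 × 3.33)/0.822 = 2.23, and the ratio is 2/2.23 = 0.90. Averaging over cases, instead of plugging in the 32%, gives 0.88 (0.82-0.96 over the five settings). Simulations gave 0.80 and 0.87, depending on the ages assumed.

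**3. Pooled crude ratio,** approximated as the infant ratio raised to the infant share:

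| Infant ratio | 10% infants | 20% infants |
|---|---|---|
| 0.60 | 0.95 | 0.90 |
| 0.88 | 0.99 | 0.97 |

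**4. After adjustment.** This is a null simulation (4 contacts a year, dispersion 1) in which all infant comparators are selected on use. The adjusted model is Poisson with age group and log(1 + baseline rate).

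| Infant share | Infant cases' rate relative to pool | Crude | Adjusted | Before-after ratio |
|---|---|---|---|---|
| 5% | 1 | 0.97 | 1.00 | 0.99 |
| 10% | 1 | 0.95 | 1.02 | 0.99 |
| 20% | 1 | 0.90 | 1.02 | 0.99 |
| 20% | 2 | 1.02 | 1.09 | 1.05 |
| 20% | 3 | 1.13 | 1.13 | 1.10 |

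Simulations with other model forms gave adjusted pooled ratios of 0.98-1.09, and 0.98-1.18 within infants. Age adjustment alone left the pooled bias in place (0.96 and 0.91 at 10% and 20% infants).

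Not all of the last two rows is due to the entry rule. With infant comparators exempt as a group, the adjusted ratios at 20% are still 1.04 and 1.07. That remainder is confounding by severity.

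**The case against.** The strongest case against is that the comparator sentence points back to the section holding the age condition, so its natural reading exempts young comparators too. If all infant comparators are exempt, and cases have the pool's rate, every ratio is about 1.00. The plan also adjusts for baseline rate, where the comparators' selecting contacts appear. Age calipers and index dates are details an article may leave to a fuller document.

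Much of this stands. The cross-reference makes the smaller figure (about 0.8-0.9) the more plausible one, and baseline adjustment removes most of the pooled bias. But the 1.00 result leaves out same-birth-year children past 6 months, and the stated match admits them on either reading. The adjustment rests on a baseline of weeks to months for these infants, not 3 years, and for selected comparators that short window contains the contacts that admitted them. The result therefore depends on model form and can overcorrect. And the gap lies in a matching rule that the article does state.

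A reader might infer that the trial will show a false benefit. The document does not support that. The ratios below 1 are crude and need infant cases to use no more care than the pool. Infants referred with medical complexity may well use more, and the bias can then run against the service. A reader might also infer that comparators under 6 months must show prior use, or that year of birth is the only matching variable. The first is one of two readings; the second is true of age only.

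**Conclusion.** The point holds as a mismatch of entry rules in one stratum of the primary comparison, with unknown direction and size. With equal underlying rates, the crude infant ratio is about 0.5-0.6 if no comparator is exempt and about 0.8-0.9 if the exemption carries over. Varying the mean and shape widens these to 0.37-0.89 and 0.82-0.96. After adjustment the pooled ratio is close to 1 but depends on the model (0.98-1.09), and it moves further above 1 if infant cases are heavier users.

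Every input is an assumption. The article does not give the share of cases under 6 months; if it is small, so is the pooled effect relative to the 20% target difference. The case for acting is that the mismatch is cheap to remove before comparators are drawn, and its sign could not be settled afterwards.

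**What to change.** 1. In the Health Service Use section, state that the age condition in the Study cohort section applies identically to comparators, judged at an index date assigned to each (for example the enrolment date of the matched case).
2. For cases enrolled under 6 months, draw comparators who are also under 6 months at that date. Match them on age in weeks or months (for example within 4 weeks), with the same diagnosis group and no use criterion.
3. Report the primary rate ratio for this stratum separately, or add a sensitivity analysis that excludes it.

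The cost is an extraction rule, month or date of birth in the linked extract, one extra stratum in the analysis, and probably fewer than 20 comparators per infant case. The change removes the selection mismatch. It does not remove confounding by severity among referred infants, which still rests on the planned covariates.

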#### Impact Evaluation: Patient and family reported outcomes data collection

In our intervention cohort, secondary child and parent reported outcomes will assess family reported experiences and parental satisfaction with care integration (PICS) [6], out of pocket expenses (adapted Mumford Scale) [7], parent and child quality of life (EQ5D5L) [8], (PedsQL4.0) [9], (CHU9D) [10] and parental wellbeing (WEMWBS) [11]. These measures and basic demographic data (e.g. date of birth, postcode for estimation of Indexes of Relative Advantage and Disadvantage [12], gender, Aboriginal and Torres Strait Islander Status) will be collected via phone and secure electronic survey by a researcher embedded in each of the LHDs, at three time points: enrolment, 6 months and 12 months later to enable longitudinal comparisons, (Table 1).

**Table 1 T1:** Family reported outcome measures.

OUTCOME MEASURES	PURPOSE

Paediatric Integrated Care Survey (PICS) [6]	Measures experiences of integration of child’s care

Adapted Mumford scale [7]	Measuring non-medical out of pocket expenses for families

EuroQol 5 Dimension 5 Level (EQ-5D-5L) [8]	Health status measure

Paediatric Quality of Life Measure (PedsQL4.0) [9]	Measuring health paediatric health outcomes

Child Health Utility 9D (CHU 9D) [10]	Instrument used to adjust quality of life years from PedsQL4.0 score for economic evaluation

Warwick-Edinburgh Mental Well-being Scale (WEMWBS) [11]	Understanding and measuring mental health and wellbeing

